### Sample size

G*Power (version 3.1.5) was used for calculating sample size. A previous study conducted on USA veterans with PTSD determined a between-group effect size of 0.59, comparing mindfulness-based intervention and present-centred therapy [48]. We hereby conservatively estimate the effect size of our study to be 0.5. Based on our previous studies on mindfulness-based intervention, we expect a 20% dropout rate at the end. Accounting for the dropout rate, and with a two-tailed $$\alpha$$error of 5%, 80% power, and 2 study groups, we will recruit 160 participants with 80 per arm.

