### Intervention: MBCT for PTSD

The intervention is MBCT with an established protocol utilised in prior studies for depression and anxiety. Minor adjustments are made to the protocol to tailor for the needs of trauma-sensitive individuals. The outline of the MBCT class is shown in Table 1. The MBCT is conducted in groups of up to 15 participants. It consists of 8 sessions with 2 h per week. Besides, to establish regular practices, a 45-minute homework per day is given to all participants. Audio recordings for home practice are provided and participants are suggested to document their practice through a given diary. Handouts and homework recordings are translated to Chinese by qualified health professionals, and are further face-validated by a group of expert mindfulness instructors. Instructors for MBCT are health professionals with formal training in mindfulness and certified to conduct MBCT. The training was referenced from the book, *Trauma-sensitive mindfulness: Practices for safe and transformative healing* [54]. This training will equip our instructors with the knowledge and skills to conduct mindfulness therapy for trauma-sensitive individuals. Several instructors instead of one will be recruited to ensure that the findings could be generalized.

**Table 1 Tab1:** Outline of MBCT program modified for this study

Session	Theme	Session content
Session 1	Awareness and Automatic pilot – identifying and stepping out of automatic pilot	Group orientation Ground rules and introduction Self-care: grounding & alert techniques to keep one in the window of tolerance, aware of own conditions, respect own limitations… Mindful eating: Raisin exercise and review Body scan practice and review
Session 2	Living in Our Heads	Body scan practice Practice and homework review Thoughts, feelings exercises with respect to PTSD symptoms Pleasant events calendar Sitting meditation
Session 3	Gathering the Scattered Mind	5-minute seeing or hearing meditation Lying down yoga stretches and review Home practice review Standing stretch and breath, body meditation, and review 3 Steps breathing space and review Unpleasant events calendar
Session 4	Recognizing Aversion	Sitting meditation and review 5-minute seeing or hearing meditation Practice and homework review Territory of PTSD and depression Breathing space and review Mindful walking and review

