### Active control: seeking safety

Seeking Safety is a manualised psychoeducational protocol developed by [name] [27]. The Chinese Version of the handouts has been translated by a group of experienced clinical psychologists from New Life Psychiatric Rehabitation Association in Hong Kong. Seeking Safety is a group intervention with a size of up to 15 participants. There are 8 sessions with a total of 2 h per week. Eight among twenty-five topics are selected for the sessions. They are “PTSD: Taking Back Your Power”, “Safety”, “Detaching from Emotional Pain (Grounding)”, “Asking for Help”, “Honesty”, “Setting Boundaries in Relationships”, “Compassion”, and “Taking Good Care of Yourself”. The selected topics were discussed with [name] to ensure the inclusion of the essential cognitive, behavioral, and interpersonal components of Seeking Safety. To encourage commitment and application of coping strategies discussed during the therapy sessions, participants could utilise the “Safe Coping sheet” and “Commitment to recovery form” if they found needed. Instructors are mental health professionals who have passed the certification test of Seeking Safety. Several instructors will be recruited to conduct the session to ensure generalisability.

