### Statistical analysis

Statistical analysis will be conducted by a statistician blinded to the group assignment of participants. The study results will be presented according to the Consolidated Standards of Reporting Trial 10 (CONSORT-10) standards. The mean, median, standard deviation (SD), interquartile range (IQR) and 95% confidence interval (95% CI) will be presented in the data description. The analysis of covariance (ANCOVA) will be the primary analysis for the primary outcome (PCL-5) and other secondary outcomes (i.e., PHQ-9, BAI, ACS, AAQ-II, RRS, FFMQ, SCSQ), with T1 score as the outcome and T0 score as the covariate. Both intention-to-treat and per-protocol analyses will be performed. For per-protocol analysis, participants who attend more than 4 classes will be considered to have satisfactory compliance. Effect size estimates will be obtained by comparing the T0 and T1 scores mean and SD, both between and within groups. For the secondary analysis, we will apply linear mixed model (LLM) to compare changes over time for PCL-5 score and other secondary outcomes between the intervention group and the active control group. Missing data will be incorporated into the LLM based on full information maximum likelihood. Mediation analysis will be done using the Baron and Kenny mediation method and structural equation modelling (SEM). The analysis will explore if the effect of mindfulness on PTSD symptoms is mediated by rumination, experimental avoidance and attentional control.

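### The sample size and the primary ANCOVA make no allowance for correlation within therapy groups, although both treatments are delivered in groups of up to 15

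*Protocol article*

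**What the plan says.** Both treatments are delivered in groups. In the section on the MBCT intervention: "The MBCT is conducted in groups of up to 15 participants". In the section on the active control: "Seeking Safety is a group intervention with a size of up to 15 participants". The Discussion repeats the group size for both arms. Each arm has several instructors; for MBCT the reason given is "Several instructors instead of one will be recruited to ensure that the findings could be generalized", and the active-control section gives a similar reason.

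The Sample size section takes a standardised effect ("We hereby conservatively estimate the effect size of our study to be 0.5"), expects 20% dropout, and concludes "with a two-tailed $$\alpha$$error of 5%, 80% power, and 2 study groups, we will recruit 160 participants with 80 per arm". It mentions no ICC, design effect or number of groups.

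The Statistical analysis section makes ANCOVA the primary analysis, "with T1 score as the outcome and T0 score as the covariate". A linear mixed model for change over time is secondary. Neither description names a term for therapy group or instructor.

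**The concern.** Participants are randomised individually, but they then spend eight 2-hour sessions with the same group and instructor. Dependence can therefore arise after allocation, and individual randomisation does not remove it. A model that ignores it takes the variance of an arm mean from the spread of individuals alone. If groups differ for reasons of their own, the standard error is too small and the two-sided 5% test rejects too often. Baseline adjustment does not protect against this: it removes variance between individuals but not a group effect that appears after randomisation.

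The test at stake is the one for superiority over an active control, which the Discussion says could lead to adoption of MBCT as a formal intervention. A positive result could owe something to one or two good groups. The sample size is already fixed on the independence basis, so a later analysis plan can restate what 160 delivers but cannot change what it was calculated for.

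**Working it through.** **Inputs from the article.** Effect size 0.5 (so SD = 1), two-sided alpha 5%, power 80%, dropout 20%, 80 per arm, groups of up to 15.

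**Assumptions, because the article gives no figure.** 64 evaluable per arm (80 × 0.8); ICC of 0.01, 0.02, 0.05 or 0.10; T0-T1 correlation r = 0.5; 6 or 10 groups per arm. Six is the minimum: 80/15 = 5.3, rounded up. Evaluable participants per group are then m = 64/6 = 10.67 or 64/10 = 6.4.

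**Step 1: the plan's own figure.** For a two-sample t-test with n per arm, the noncentrality is 0.5 × √(n/2) on 2n − 2 degrees of freedom (df). At n = 63 power is 79.5%; at n = 64 it is 80.1%. Then 64/(1 − 0.20) = 80 per arm, 160 in total. The match is exact, so the design effect used was 1.

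**Step 2: design effect.** DE = 1 + (m − 1) × ICC. With 6 groups: 1.10, 1.19, 1.48, 1.97. With 10 groups: 1.05, 1.11, 1.27, 1.54.

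**Step 3: type I error of the planned ANCOVA.** With the ICC as a share of total variance, the adjusted variance of an arm mean is v/64, where v = (0.75 − ICC) + m × ICC and 0.75 = 1 − r². The ANCOVA works with about 0.75/64. The error rate is 2 × [1 − Φ(1.96 × √(0.75/v))]. Example, 6 groups, ICC 0.05: v = 0.70 + 0.533 = 1.233; √(0.75/1.233) = 0.780; 1.96 × 0.780 = 1.528; error 12.6%. Simulation of the planned ANCOVA (20,000 null trials per setting) agrees, and gives about 5% at ICC 0.

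**Step 4: power of a valid test.**

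(a) On the plan's own basis (no baseline gain, individual-level df): noncentrality 0.5 × √(64/(2 × DE)).

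(b) With r = 0.5 and group-level df (10 for 6 groups per arm, 18 for 10): noncentrality 0.5 × √(64/(2 × 0.75 × DE)). Example, 6 groups, ICC 0.05: 0.5 × √(64/(1.5 × 1.483)) = 2.68 on 10 df, power 68%.

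| ICC | 0.01 | 0.02 | 0.05 | 0.10 |
|---|---|---|---|---|
| Type I error, 6 groups per arm | 6-7% | 8% | 12-13% | 19-20% |
| Type I error, 10 groups per arm | 6% | 7% | 9% | 14% |
| Power (a), 6 groups | 76% | 73% | 64% | 52% |
| Power (b), 6 groups | 80% | 77% | 68% | 56% |
| Power (b), 10 groups | 85% | 84% | 78% | 70% |

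Row (b) multiplies the whole variance by 0.75, so it lets baseline adjustment shrink the group effect as well. If only the individual part shrinks, v from step 3 replaces 0.75 × DE, and row (b) becomes 79%, 75%, 63% and 50% with 6 groups and 85%, 82%, 76% and 65% with 10.

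**The case against.** The strongest reply is that everything beyond step 1 depends on quantities the article does not give. That is right, and it limits the point in several ways.

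- A reader might infer that the 80% power and 5% error are certainly not delivered. The documents do not support that. At ICC 0 both hold; at ICC 0.01 with r = 0.5 a valid test still has about 80% power with 6 groups.
- A reader might take 6 groups per arm as the design. Fifteen is a ceiling, and the Discussion describes classes in different districts, on weekday nights and at weekends. More and smaller groups are plausible, and they soften the effect.
- It is tempting to quote power on 10 df without baseline gain: 68%, 65%, 56% and 45%. That mixes two effects. The 10-df reference alone gives 72% at ICC 0, and the planned ANCOVA does adjust for baseline.
- The article does not say that the mixed model treats participants as independent. Its random effects are not described, and such detail is often left to an analysis plan. All that can be said is that no group or instructor term is named.
- Instructors may be nested in arm, since each arm's instructors hold that arm's certification, but the article does not say that nobody holds both.
- Using several instructors to help generalise is a reason for recruiting them, not a stated promise of inference to a population of instructors.

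It might also be said that the ANCOVA as planned still rejects often enough. In simulation at an effect of 0.5 with 6 groups it rejected in 88%, 84% and 81% of trials at ICC 0.01, 0.05 and 0.10, but at the higher ICCs it stays above 80% only because the error rate is inflated.

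What remains is that the sample size was computed with a design effect of 1, the stated primary model has no group term, and nothing elsewhere in the article makes up for either.

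**Conclusion.** The point stands in conditional form and should be fixed. That 160 contains no allowance for clustering is shown by exact reproduction. That the primary ANCOVA names only the T0 score is stated in the text. The consequence depends on the ICC, the number of groups and the baseline correlation, all of them assumed here. At ICC 0.01-0.02 the error rate is about 6-8% and the power loss is modest or offset by baseline adjustment. At ICC 0.05-0.10 the error rate is about 9-20%, and the power of a valid test is about 56-78% under r = 0.5 and group-level df, somewhat lower if adjustment does not shrink the group effect. Because the serious end needs ICCs that the article does not document, this is a recommended correction rather than a proven failure of the primary test.

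**What to change.** 1. Record a therapy-group identifier and an instructor identifier for every participant while the groups are running; they may be hard to recover later.
2. In the Statistical analysis section, add a random intercept for therapy group, nested in arm, to the primary baseline-adjusted model and to the linear mixed model, with Kenward-Roger or Satterthwaite degrees of freedom.
3. In the Sample size section, keep N=160 and restate its power for that model over a stated range of ICC, number of groups per arm and T0-T1 correlation.

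The cost is wording, two data fields, possibly wider confidence intervals and possibly a less favourable power statement. No extra participants are needed.

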### Ethical concern

Information about this study, including procedures, objectives, study period and randomisation arrangement will be provided to participants. Participants will be given time to consider whether or not they want to join the study. Once agreed, they will be asked to sign the informed consent with a duplicate copy kept by the research team members. Participants’ information and data will be kept in a password-protected computer and can be only assessed by responsible team members. Participants could choose to discontinue the study at any time. In case of adverse events, participants could seek help from the research team and the team will arrange for physicians certified in psychiatric practice or psychologists for further follow-up. All adverse events will be reported to the ethics committee immediately. The outcome of this study will be published in peer-reviewed journals and announced in public conferences according to the CONSORT-10 standards.

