Most guidelines recommend manualized trauma-focused psychotherapies as the first-line treatment for PTSD [22]. On the other hand, medications could be used to assist treatment of PTSD symptomology [22]. Recommendations for PTSD medications might differ across guidelines [23]. In general, SSRIs outperform other medications and their efficacy has been evaluated in several studies [24]. However, meta-analysis studies found pharmacological intervention not as effective as psychotherapy [25]. A manualized psychotherapy contains guided standards for psychologists or psychiatrists to follow while ensuring that all trauma topics are well addressed. Over the years, several psychotherapeutic approaches have been developed to target PTSD. Examples are narrative exposure therapy, cognitive reprocessing therapies, eye-movement systematic desensitization and reprocessing and cognitive-behavioural therapy [22]. Psychotherapies mainly focus on the re-processing of traumatic memories, psychoeducation of coping skills and emotional regulation [26]. Seeking Safety is an evidence-based manualized psychological treatment. Its protocol was developed by [name] in the early 2000s that targets PTSD and substance abuse [27]. The core idea of Seeking Safety is to establish “Safety”. The word “Safety” here is an umbrella term that contains multiple elements: reducing suicidality, establishing safe relationships, taking good care of self, maintaining healthy habits etc [28]. . The whole protocol of Seeking Safety consists of 25 topics. These topics covers cognitive, behavorial and interspersonal domains. Examples of topics are “Safety”, “Compassion”, “Honesty”, “Asking for Help”, “Commitment”, “Creating meaning” etc. However, therapists can personalise and select suitable topics in the treatment manual. Over the past 20 years, various studies have been conducted showing that Seeking Safety could reduce PTSD symptoms significantly among different populations [29–31]. While the above treatments are evidence-based and recommended for PTSD, several concerns have been raised in various studies. First, there remains a certain level of dropout rate in trauma-focused psychotherapy, with the pool dropout rate at 16% [32]. Potential reasons for dropout might be treatment intolerance and symptom exacerbation due to traumatic reminders [33]. Besides, some psychologists have expressed concern about trauma-focused psychotherapy as this approach requires patients to unveil their trauma to the therapist [34]. Moreover, most of them retain the residual symptoms with the persistent diagnosis of PTSD after therapy [35]. Therefore, more alternative approaches are needed for managing PTSD.

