### Outcome measures

Demographic information will be collected at baseline, including their gender, age, education, income, marital status, medical history, medication, and types of traumatic events. Primary and secondary outcomes will be collected by a research assistant who is blinded to the group assignment at T0, T1 and T2 through questionnaires. In addition, participants from both groups will be asked to fill out a course evaluation at T1. Participants assigned to MBCT will fill out an extra section on their questionnaire indicating their mindfulness practice habits at T1 and T2. The primary and secondary outcome measures are shown below.

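### The only route described for adverse events is the participant's own initiative, so harms may be under-counted; one identical question at T1 and T2 would remedy this cheaply

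*Protocol article*

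**What the plan says.** The Protocol article deals with adverse events under Ethical concern, in three steps:

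- Entry: "In case of adverse events, participants could seek help from the research team".
- Care: "the team will arrange for physicians certified in psychiatric practice or psychologists for further follow-up".
- Onward reporting: "All adverse events will be reported to the ethics committee immediately".

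Outcome measures sets out what is collected after baseline. "Primary and secondary outcomes will be collected by a research assistant who is blinded to the group assignment at T0, T1 and T2", by questionnaire. In addition, "participants from both groups will be asked to fill out a course evaluation at T1"; the content of that evaluation is not given. MBCT participants also complete a section on their practice habits at T1 and T2. No item on harm is described.

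Two other places bear on the point. Among the limits of existing trauma-focused therapy, the Introduction names "treatment intolerance and symptom exacerbation due to traumatic reminders" as possible reasons for dropout, and goes on to argue for alternatives. Under Intervention: MBCT for PTSD, the article says: "Minor adjustments are made to the protocol to tailor for the needs of trauma-sensitive individuals".

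**The concern.** The article undertakes to report every adverse event, but the one entry point it describes depends on the participant coming forward. A person who feels worse and stops attending has least contact with the team and may be least likely to do so. Events missed in this way cannot be reconstructed after T2.

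The consequence would be a harms count of unknown completeness. A low or zero count could then be read as evidence of good tolerability when it shows only that few people volunteered a report. This matters because tolerability of existing therapy is part of the background to the trial, MBCT was adapted with trauma sensitivity in mind, and the results are meant to inform intervention guidelines.

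A second, lesser issue is that deterioration can be hidden in a comparison of means. Statistical analysis describes ANCOVA on T1 scores and a mixed model for change over time. Either could favour MBCT on average while some participants worsen.

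**Working it through.** **The plan's own figure.** The article gives no number for adverse events, so the relevant stated figure is the sample size. Inputs from Sample size: effect size 0.5, two-tailed 5%, power 80%, dropout 20%. A two-sample t-test (noncentral t) needs 63.8, so 64 per arm. Then 64 / (1 − 0.20) = 80 per arm, 160 in total. This reproduces the plan, and nothing below changes it.

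**Comparison of sections.**

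| Step | What is described | Where |
|---|---|---|
| Event becomes known | Participant may approach the team | Ethical concern |
| Event is managed | Physician or psychologist arranged | Ethical concern |
| Event is reported | All, immediately, to the ethics committee | Ethical concern |
| Scheduled data at T1 and T2 | Outcome questionnaires; course evaluation (T1 only); practice section (MBCT only) | Outcome measures |
| Enquiry about harm at T1 or T2 | None described | – |

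The reporting duty covers all events, but the only described source is self-referral. T1 and T2 already provide scheduled contact with both arms at which a question could be asked.

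**What incomplete capture would do.** The article gives neither event rates nor capture fractions. All of those below are assumptions, used to show sensitivity.

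1. *Zero events in an arm of 80.* One-sided 95% upper bound with full capture: 1 − 0.05^(1/80) = 3.68%. The recorded rate equals the true rate times the capture fraction, so the bound on the true rate is 3.68% / capture. At 50% capture this is 7.4%; at 30% it is 12.3%.

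2. *Chance of recording at least one event in 80*, 1 − (1 − rate × capture)^80:

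| True rate | Full capture | Half | Quarter |
|---|---|---|---|
| 2% | 80% | 55% | 33% |
| 5% | 98% | 87% | 63% |

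3. *Power to see a true difference of 10% against 20%*, 80 per arm, two-sided 5%. Power = Φ{[|p1 − p2| − 1.96·√(2p̄(1 − p̄)/n)] / √([p1(1 − p1) + p2(1 − p2)]/n)}, with each rate multiplied by the capture fraction:

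| Capture | Expected counts | Power |
|---|---|---|
| Full | 8 vs 16 | 42% |
| Half | 4 vs 8 | 22% |
| Quarter | 2 vs 4 | 13% |

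4. *Silence among those who leave.* The planned 20% dropout is 16 of 80 per arm. Suppose leavers report nothing and all others report everything. With the same event rate in both groups, 16/80 = 20% of events are lost. With 20% among leavers and 10% among the other 64, events number 16 × 0.20 = 3.2 and 64 × 0.10 = 6.4, so 3.2 / 9.6 = 33% are lost.

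**Worsening.** PCL-5 is recorded at T0, T1 and T2 in both arms, so the proportion whose score has risen can be derived without new data collection.

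**The case against.** The strongest reply is that the quoted sentence describes access to care, not a method of ascertainment. It stands in an ethics section, and the commitment to report all events is not limited to those that participants raise. Adverse-event forms may sit in the full protocol and worsening tables in an analysis plan, neither of which is shown. The course evaluation at T1 might itself ask about harm. Harms are also absent from the objectives and hypotheses.

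Much of this stands. A reader might infer that events are captured exclusively by self-report, that nobody is asked about harm, or that under-counting is certain. The text supports none of these; it supports only that no other route is described and that under-counting is possible.

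A reader might also infer that capture differs by arm, because MBCT reviews home practice in sessions 2 to 8 while the Seeking Safety sheets are optional. The document does not support this either. The same route is described for both arms, and scheduled contact is matched at eight weekly two-hour sessions in groups of up to 15. For Seeking Safety only topics and sheets are listed, so the article does not show that participants' difficulties go unreviewed there. Nor does the Introduction's remark on symptom exacerbation predict harm from MBCT or Seeking Safety; it concerns trauma-focused psychotherapy.

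What the reply does not remove is that the article sets out an adverse-event process from entry to reporting and also lists the T1 and T2 data. The entry point it chose to describe is passive. That is a stated route open to improvement, not merely a missing detail.

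**Conclusion.** The point holds in limited form. As described, adverse events reach the team on the participant's initiative, and no enquiry about harm appears among the T1 and T2 assessments. Harms may therefore be under-counted, most plausibly among those who stop attending. Neither the amount nor any imbalance between arms can be computed from the document. The figures above rest entirely on assumed event rates and capture fractions, and show only that incomplete capture would matter if it occurred.

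The primary comparison and the sample size of 160 are untouched. The reason to act is timing and cost: the enquiry is easy to add while T1 and T2 lie ahead and cannot be added afterwards. The table of PCL-5 worsening is secondary, since it can be produced later from stored data and may already be planned elsewhere.

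**What to change.** 1. Add one adverse-event question, identically worded, to the T1 and T2 questionnaires in both arms, and put it also to participants who have stopped attending. If the full protocol or the course evaluation already contains such a question, say so and confirm that it is the same in both arms and at both times.
2. Have the item self-completed, or handled by someone other than the outcome assistant, so that answers mentioning meditation or session topics do not unblind that assistant.
3. Tabulate the answers by arm, with the number who answered as the denominator.
4. As a supporting step, report by arm the proportion whose PCL-5 exceeds the T0 value by one amount fixed before unblinding, at T1 and at T2. The article gives no such amount; the investigators should choose and justify it.

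The care pathway in Ethical concern stays as it is. The cost is one questionnaire item, one table and probably more events to forward to the ethics committee. No staff, visits or participants are added.
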